**Table 4 Groups involved in the 2 phases of the clinical trial**

| Phase II | n  | LTBI/HIV-                         | n  | LTBI/HIV+                         |
|----------|----|-----------------------------------|----|-----------------------------------|
|          | 12 | RUTI ® (5µg of FCMTb)  | 12 | RUTI ® (5µg of FCMTb)  |
|          | 12 | RUTI ® (25µg of FCMTb) | 12 | RUTI ® (25µg of FCMTb) |
|          | 12 | RUTI ® (50µg of FCMTb) | 12 | RUTI ® (50µg of FCMTb) |
|          | 12 | placebo                           | 12 | placebo                           |

The medication (RUTI® vials) will be prepared giving the vero or placebo after the random attribution to a serial number. The randomization list will be sent to the persons responsible of the medication storage and labelling and the rest of the personnel will be kept blinded.

Medication will be transferred to pharmacists at each trial site with the correspondent sealed envelope labelled with the serial number containing information on the nature of the medication inside. This envelope will be opened only in case of necessity (i.e. toxicity), and the reason/s, the responsible/s, time and signature/s will be included in a form.

The investigators will follow the trial's randomization procedures, and will ensure that the code will only be broken in accordance with the protocol. In case of any premature unblinding of the investigational product (e.g. accidental unblinding, unblinding due to a serious adverse event (SAE)) they will promptly document and explain it to the sponsor.

Stratification will be required for this trial.

If one subject withdraws from the clinical trial before receiving the first RUTI® or Placebo inoculation, he/she will be replaced by another subject to complete the trial intended numbers, except if the trial has to be ended because of safety issues or the total number of subjects having received at least one inoculation is reasonably sufficient to achieve the study objectives. This new subject will receive the corresponding medication that the one replaced would have received and will be assigned to the corresponding identification subject code.

### 3.4 Description of the Trial Treatments and the Dosage and Dosage Regimen of the Investigational Product. Dosage Form, Packaging, and Labeling of the Investigational Product

The trial drug is RUTI® vaccine, and the drug substance is a detoxified, pasteurized mixture of different protein antigens and lipids from fragmented cells of *M. tuberculosis* strain 511 FCMtb.

RUTI vaccine is presented as a dry powder for reconstitution containing 66.7 µg of FCMtb per vial in a liposomal lyophilised formulation.

The qualitative and quantitative composition per vial of RUTI® vaccine is shown next table (Table 5):

**Table 5 The qualitative and quantitative composition per vial of RUTI® vaccine**

| COMPONENTS                   | UNIT PER VIAL | FUNCTION                                           |
|------------------------------|---------------|----------------------------------------------------|
| DRUG SUBSTANCE        |               |                                                    |
| FCMtb                        | 66.7 µg       | Immunogen                                          |
| EXCIPIENTS            |               |                                                    |
| Sucrose                      | 20000.0 µg    | Charge substance (freeze-drying) and cryoprotector |
| Soy lecithin     | 845.8 µg      | Liposome forming agent                             |
| Sodium cholate               | 92.0 µg       | Tensoactive                                        |
| Sodium chloride  | 20.8 µg       | Solvent                                            |

 Containing Phosphatidylcholine (NLT 94.0%)

 Added as NaCl 0.9% solution.

RUTI® vaccine is formulated to be administered by subcutaneous route after reconstitution with water for injection (0.4 mL) to give a suspension containing 166.7µg /mLof FCMtb. Next table (Table 6) shows the concentration of each component per vial after reconstitution.

**Table 6 The concentration of each component per vial after reconstitution**

| Components            | Concentration per vial |
|-----------------------|------------------------|
| DRUG SUBSTANCE |                        |
| FCMtb                 | 166.7 µg/mL            |
| EXCIPIENTS     |                        |
| Sucrose               | 50,000.0 µg/mL         |
| Soy lecithin          | 2,114.4 µg /mL         |
| Sodium cholate        | 230.0 µg /mL           |
| Sodium chloride       | 52.1 µg /mL            |

RUTI® vaccine is manufactured by ARCHIVEL FARMA, S.L. (Badalona. Catalonia, Spain) under GMP.

The manufacturing process of RUTI® has been published elsewhere (7). Briefly, *M. tuberculosis* are cultured for three weeks in Middlebrook 7H11 agar at 37°C, under a progressive conditions

of low pH and pO2. Colonies are carefully removed and mechanically disrupted using silica-zirconium beads and a PBS buffer with 4% Triton-X114. After centrifuging at 845 g to remove the entire cells, the pellet is centrifuged at 20,000 g, the lipidic supernatant is discarded and the final product is washed, pasteurized at 65°C for 60 minutes, and lyophilized.

The freeze-dried drug substance will be finally formulated as liposome drug product. To do this liposome preparation is undertaken after mixing at high speed (lipid phase of the liposomes consisting of soy lecithin solution, sodium cholate solution, and the drug substance FCMtb; the aqueous phase consisting of saline solution (NaCl) diluted with bidistilled apyrogenic water). As charge substance, 5% sucrose is used.

### **Dosage and Administration**

A total of three doses of RUTI® vaccine will be tested: 5, 25 and 50µg of FCMtb, chosen from the Phase I clinical trial experience in terms of tolerability and polyantigenic immune response.

A single dose of the vaccine or placebo (0.3 mL) will be administered twice to the subjects, 28 days apart (on days 28 and 56), by subcutaneous route, after one-month of INH pre-treatment. Sites of injection will be alternated (i.e., the injection should be given subcutaneously in the deltoid muscle area [right or left] that is opposite to the previous injection site). Both the injection site and the opposite deltoid muscle should be evaluated during the course of the trial. The exact date and times of each trial drug administration will be recorded in the CRF together with the side of the injection (right or left deltoid muscle).

Subjects will be followed-up for safety and immunogenicity parameters until the end of the trial

### **Packaging and Labelling**

The trial drug will be packaged in vials containing the active substance and excipients as indicated in [Table 5](#) ~~Table 5~~. Placebo will be packaged in the same type of vials containing identical amount of excipients without active substance. The vials will be labelled RUTI® or placebo, respectively. Before administration, the pharmacist of the pharmaceutical departments at each site, as designee of the principal investigator, will reconstitute and dilute the content of the vials according to the dose assigned to each subject. Therefore, the pharmacist will not be blinded. The pharmacist will label the administration syringe with the subject's randomization number. For these processes, the pharmaceutical departments at each site adhere to specific rules as described in the Good Manufacturing Practice (GMP) Annex 13 requirements.

### Preparation and Handling

The trial drug will be packaged in vials containing the active substance and excipients as indicated in [Table 5](#)~~Table 5~~. Placebo will be packaged in the same type of vials containing identical amount of excipients without active substance. The vials will be labelled RUTI® or placebo, respectively. Before administration, the pharmacist of the pharmaceutical departments at each site, as designee of the principal investigator, will reconstitute and dilute the content of the vials according to the regimen (trial drug or placebo) and dose assigned to each subject. Therefore, the pharmacist will not be blinded. The pharmacist will label the administration syringe with the subjects' randomization number. For these processes, the pharmaceutical departments at each site adhere to specific rules as described in the Good Manufacturing Practice (GMP) Annex 13 requirements.

### Preparation and Handling

The trial drug (and placebo) will be stored between 2° - 8°C in the pharmaceutical departments at each site until reconstitution proceeds.

Allow the trial drug and placebo to equilibrate at room temperature for at least 5-10 minutes before reconstituting it with sterile water for injection. Mix thoroughly and gently to minimize frothing in order to ensure complete resuspension. After convenient dilution accordingly with the Working Document, a total volume of 0.3 mL will be administered subcutaneously.

### 3.5 Expected Duration of Subject Participation

Each subject will be screened within the 28 days period prior to Visit 1 (Day 0). Should the screening period be longer than 28 days subjects may be re-screened after agreement between the sponsor and the investigator. After the inclusion in the trial (d0), the subjects will remain in the trial for 84 days. See [Figure 18](#)~~Figure 18~~.

### 3.6 Stopping Rules or Discontinuation Criteria for Individual Subjects, Parts of Trial and Entire Trial

An independent monitoring committee, the Data Safety Monitoring Committee (DSMC), will be established to monitor the trial subjects, and to assess the progress of the clinical trial and the safety data. The DSMC will meet at predetermined intervals to review the unblinded results.

As its main objective is the safety of the patient, the DSMC will make important trial-related decisions. They will decide whether to withdraw a subject for safety reasons and will recommend to the sponsor whether to continue, modify or stop the clinical trial.

Every decision of the DSMC will be taken after consensus of all the members of the committee.

### **3.7 Drug Accountability Procedures**

The clinical investigator or designee is responsible for ensuring that all trial drug received at Pharmaceutical Services is inventoried and accounted for throughout the trial. The dispensing of trial drug to the subject will be documented on the drug accountability form. Unused or partially used trial drug will be stored and disposed of according to the sponsor's instructions. Contents of the trial drug containers must not be combined.

Trial drug must be handled strictly in accordance with the protocol and the container label and will be stored in a limited access area under appropriate environmental conditions. Unused trial drug must not be disposed of until the sponsor's monitor has completed drug accountability during an on-site monitoring visit. The return to the sponsor or destruction on-site of used and unused trial drug will be documented on the Drug return form.

Trial drug will be dispensed under the supervision of the investigator, or a qualified member of the investigational staff. Trial drug will be supplied only to subjects participating in the trial. Trial drug will not be re-labelled or reassigned for use by other subjects. The investigators agree to dispense the trial drug only at the Clinical Units agreed upon with the sponsor.

### **3.8 Randomization and Maintenance of Trial Treatment Randomization Codes and Procedures for Breaking Codes**

A randomization schedule will be provided by Biostatistics from Clinical Data Services of PAREXEL International (South Africa), Bloemfontein. The randomization schedule will be generated using RANDPLAN, a locally developed SAS® macro utilizing PROC PLAN procedure in SAS® (8).

The investigators, ARCHIVEL FARMA, S.L, and any personnel involved in subjects' assessment, monitoring, analysis and data management will be blinded to the subject assignment. Treatments will be packaged by the pharmaceutical departments at each site and/or designee and supplied to the investigator as identical-appearing treatments.

Two copies of emergency code break envelopes will be prepared, one copy for the ARCHIVEL FARMA, S.L. and one copy to be kept at the pharmacy. The envelopes should be maintained in a secure locked place throughout the trial while still allowing access for emergency code breaking. In case of a medical emergency, when the trial drug assignment is needed to make treatment decisions for the subject, the investigator may unblind the subject's drug assignment. ARCHIVEL FARMA, S.L. and the medical monitor should be notified of the event prior to breaking the code, if possible. If this is not possible, ARCHIVEL FARMA, S.L. should be notified immediately afterwards, and the subject's drug code assignment should not be revealed. The circumstances leading to the breaking of the code should be fully documented, in the investigator's trial files and in the subject's source documentation. In studies conducted in the EU, for AEs that are defined as: Suspected Unexpected Serious Adverse Reaction (SUSAR), ARCHIVEL FARMA, S.L. or designee may break subject's code for possible regulatory submission.

All randomization code break envelopes will be collected and returned to ARCHIVEL FARMA, S.L. or designee at the completion of the trial.

## **4. SELECTION AND WITHDRAWAL OF SUBJECTS**

### **4.1 Inclusion Criteria**

Subjects who meet the following criteria will be considered eligible to participate in the clinical trial:

1. Asymptomatic adult aged 18 up to 50 years.
2. No evidence of active TB (Section 8).
3. No clinically significant finding at the discretion of the investigator.
4. Willingness to undergo an HIV test.
5. Resident in or near trial site for the duration of the trial.
6. Willingness to allow the investigators to discuss the patient's medical history with his usual doctor or HIV physician.
7. No donation of blood for 56 days prior to screening and agreement to refrain from blood donation during the trial.
8. Willing and able to provide written informed consent.
9. Positive tuberculin skin test (TST +), ( $\geq 5$  mm induration) and QuantiFERON TB Gold positive result (according to manufacturers instructions).
10. Reliable contraception to be used by female subjects during the clinical trial.
11. Additional inclusion criteria for HIV+ groups:
  - HIV antibody positive.
  - CD4 count  $\geq 350$  cells/mL on a single CD4 count at the period of screening.
  - Subjects on anti-retroviral treatment can be included if clinically stable.

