### **4.2 Exclusion Criteria**

Subjects who meet one or more of the following criteria will not be considered eligible to participate in the clinical trial:

1. Any deviation from the normal range in biochemistry or haematology blood tests or in urine analysis that is considered to be clinically significant at the discretion of the

investigator. Values of Hb, WCC, platelet count, AST/ALT and creatinine should be in a normal range accordingly to the normal laboratory values.

2. Use of any investigational or non-registered drug, vaccine, or medical device other than the trial vaccine within 30 days prior to dosing of trial vaccine, or planned use during the trial period.
3. Administration of chronic (defined as more than 14 days) immunosuppressive drugs within six months of vaccination and required throughout the duration of the trial (for corticosteroids this means prednisolone or equivalent at  $\geq 0.5$  mg/kg/day).
4. Female of child bearing potential who intends to become pregnant during the trial.
5. Females who are pregnant, lactating, or of child bearing potential with a blood HCG positive result 24-48 hours at the screening period, or prior to every injection of RUTI®.
6. Any AIDS defining illness according to the CDC classification system for HIV infection (Appendix 17.1).
7. Presence of active (previously undiagnosed) TB or being on TB treatment.
8. Suspected or known current alcohol abuse (alcohol intake questionnaire, Appendix 17.2).
9. Suspected or known substance abuse.
10. Presence of any underlying disease, specifically autoimmune disease, asthma, angioedema, bleeding disorders, uncontrolled hypertension and diabetes, and any other disease that compromises the diagnosis and evaluation of response to the vaccine, excluding HIV.
11. Administration of immunoglobulins and/or any blood products within three months prior to the planned administration of the vaccine.
12. Any history of anaphylaxis in reaction to vaccination and/or other medication.
13. Investigator assessment of lack of understanding or willingness to participate and comply with all requirements of the trial protocol.
14. Any other finding which in the opinion of the investigator would significantly increase the risk of having an adverse outcome from participating in the trial.
15. Exclusion criteria relating to INH pre-treatment
  - Weight less than 40 kg.

- Known or suspected hypersensitivity to INH.

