- Self reported chronic liver disease or symptoms suggesting active hepatitis (jaundice, nausea, vomiting, right upper quadrant pain, dark urine, pale stools).
- Alcohol use exceeding 28 units per week (men) or 21 units per week (women) (see alcohol intake questionnaire, Appendix 17.2).
- History of convulsions.
- History of psychosis.
- Peripheral neuropathy grade 2 or greater.
- Three months post-partum.
- Concomitant medication with phenytoin, carbamazepine; warfarin; theophylline; disulfiram; selective serotonin re-uptake inhibitor antidepressants (e.g. citalopram, fluoxetine, paroxetine, sertraline); oral ketoconazole or itraconazole.

16. Additional exclusion criterion for HIV negative groups:

- Any confirmed or suspected immunosuppressive or immunodeficient condition, including asplenia.

17. Additional exclusion criterion for HIV+ groups

- CD4 count < 350 cells/mL.

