## 17. APPENDICES

### 17.1 CDC Classification System for HIV Infection

The CDC categorization of HIV/AIDS is based on the lowest documented CD4 cell count (Table 1) and on previously diagnosed HIV-related conditions (Tables 2 and 3). For example, if a patient had a condition that once met the criteria for Category B but now is asymptomatic, the patient would remain in Category B. Additionally, categorization is based on specific conditions, as indicated below. Patients in categories A3, B3, and C1-C3 are considered to have AIDS.

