**Table 1. CDC Classification System for HIV-Infected Adults and Adolescents**

| CD4 Cell Categories  | Clinical Categories                  |                                           |                                 |
|----------------------|--------------------------------------|-------------------------------------------|---------------------------------|
|                      | A
Asymptomatic, Acute HIV, or PGL | B
Symptomatic Conditions,#* not A or C | C
AIDS-Indicator Conditions* |
| (1) ≥500 cells/μL    | A1                                   | B1                                        | C1                              |
| (2) 200-499 cells/μL | A2                                   | B2                                        | C2                              |
| (3) <200 cells/μL    | A3                                   | B3                                        | C3                              |

Key to abbreviations: CDC = U.S. Centers for Disease Control and Prevention; PGL = persistent generalized lymphadenopathy.

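### The CD4 cut-off for the HIV+ groups is printed in cells/mL in both eligibility lists, while Appendix 17.1 counts CD4 cells per μL; taken literally, the cut-off screens out practically no one

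*Protocol*

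**What the plan says.** The HIV+ groups have two mirrored CD4 criteria in the protocol.

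- Section 4.1, inclusion criterion 11, requires a count of at least 350, given as "cells/mL on a single CD4 count at the period of screening".
- Section 4.2, exclusion criterion 17, rules out a "CD4 count < 350 cells/mL".

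The protocol gives a CD4 scale in one other place. Table 1 of Appendix 17.1 has three bands: "1) ≥500 cells/μL", "2) 200-499 cells/μL" and "3) <200 cells/μL". This appendix is tied to eligibility, because exclusion criterion 6 rules out "Any AIDS defining illness according to the CDC classification system for HIV infection (Appendix 17.1". The introduction to the appendix adds: "Patients in categories A3, B3, and C1-C3 are considered to have AIDS". Categories A3 and B3 are those in the lowest CD4 band.

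No section corrects the unit in the two criteria or explains why it differs from the appendix.

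**The concern.** The two criteria agree with each other, so comparing them does not show that anything is wrong. The mismatch appears only when they are set against the appendix. The protocol then uses two CD4 scales that differ by a factor of 1000, and both bear on who may enter the HIV+ half of the trial.

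Three things are at stake.

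- **Safety.** Safety and tolerability are the primary endpoint (Section 3.1). The completed human study that the protocol describes was in healthy volunteers (Section 1.2), so the lower limit on immune status in the HIV+ groups should not be open to interpretation.
- **Interpretation.** The secondary endpoint is a cellular immune response, and Section 1.5 presents the HIV- subjects as the comparison for the HIV+ response. That comparison needs a clearly defined HIV+ stratum.
- **Operation.** Section 9.1 provides for automatic range and consistency checks. A check programmed to the printed unit would practically never fire. A check programmed in cells/μL would contradict the approved text.

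**Working it through.** **Inputs**

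- Cut-off as printed: 350 cells/mL (inclusion criterion 11 and exclusion criterion 17).
- Band boundaries in Appendix 17.1, Table 1: 500 and 200 cells/μL.
- Conversion: 1 mL = 1000 μL.
- HIV+ stratum: 48 of 96 subjects (Section 9.6).

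**Step 1: the printed cut-off on the appendix scale.** 350 cells/mL ÷ 1000 μL/mL = 0.35 cells/μL.

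**Step 2: distance from the appendix bands.**

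- 200 ÷ 0.35 = 571, so the printed cut-off is about 571 times below the boundary of the lowest band.
- 500 ÷ 0.35 = 1,429, so it is about 1,429 times below the boundary of the highest band.
- The number 350 read in cells/μL is 350 × 1000 = 350,000 cells/mL, a factor of exactly 1000. On that reading it lies inside the middle band.

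**Step 3: which counts pass under each reading.**

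| CD4 count (cells/μL) | In cells/mL | Passes as printed (≥ 350 cells/mL) | Passes if 350 is read in cells/μL |
|---|---|---|---|
| 1 | 1,000 | yes | no |
| 50 | 50,000 | yes | no |
| 199 | 199,000 | yes | no |
| 200 | 200,000 | yes | no |
| 349 | 349,000 | yes | no |

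**Step 4: do other criteria fill the gap?**

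- Exclusion criterion 6 refers to an AIDS-defining illness. If the appendix's AIDS categories are read into it, counts below 200 cells/μL (A3 and B3) are excluded. A low count alone is not plainly an illness, so this reading can be disputed. Even when it is accepted, it does not reach 200 to 349 cells/μL.
- Exclusion criterion 10 (underlying disease) leaves HIV out.
- Exclusion criterion 16 (immunodeficient conditions) applies only to the HIV- groups.
- Exclusion criterion 1 asks for a normal white cell count but sets no CD4 limit.
- Inclusion criteria 1 and 3 (asymptomatic; no clinically significant finding) and exclusion criterion 14 (any other risk-raising finding) can keep a subject out, but they rest on symptoms or the investigator's judgement and not on a CD4 count.

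So on the printed unit, and on the widest reading of exclusion criterion 6, no stated CD4 limit stops a subject at 200 to 349 cells/μL.

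**The case against.** The strongest reply is that this is an obvious slip. A limit of 0.35 cells/μL would make both criteria pointless, the usual scale is printed in the same protocol, and 350 fits naturally within it. Nothing suggests that screening staff or the laboratory would work in cells/mL, so sites would probably read through it. This stands as a limit on the practical risk. It does not make the text right: an operative eligibility rule should not depend on each site correcting it silently.

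The printed unit might also be an artefact of reading the PDF, with a μ turned into an m. That is unlikely, because the same text shows the symbol correctly in Appendix 17.1 and in the dose units, and the cells/mL form appears in two separate criteria. The source page settles it quickly.

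A reader might infer more than the protocol supports:

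- **That the eligibility criteria as a whole exclude practically no HIV+ subject.** This holds only for the CD4 criterion. The other criteria in step 4 still limit entry, and exclusion criterion 6 arguably covers counts below 200 cells/μL.
- **That 48 subjects are affected.** That is the size of the HIV+ stratum. The protocol gives no CD4 distribution from which to estimate how many entrants would fall below 350 cells/μL.
- **That the Per Protocol population would change.** Section 9.9 leaves the detailed exclusion reasons to the SAP and the blind data review, and the SAP is not available here. Section 9.3.1 only lists CD4 counts, and the ANCOVA in Section 9.3.2 uses no CD4 cut-off. An effect on the analysis sets or on the immunogenicity results is possible but not shown.

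**Conclusion.** The point holds as a unit error in an operative eligibility threshold. The size of the discrepancy is exact: the printed cut-off is 0.35 cells/μL, a factor of 1000 from the same number on the scale of Appendix 17.1. Read literally, the CD4 criterion does practically nothing. The part left without any stated CD4 limit is 200 to 349 cells/μL if exclusion criterion 6 is read to include categories A3 and B3, and extends further down if it is not.

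The conclusion rests on the two criteria being printed in the source as they appear here. The likely practical effect is smaller than the factor suggests, because sites would probably apply the number on the usual scale. The number of subjects affected is unknown. The error still needs correcting before screening, since it concerns safety and the literal text gives no basis for calling a low-CD4 enrolment a deviation.

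**What to change.** Reconcile the unit in inclusion criterion 11 and exclusion criterion 17 with Appendix 17.1 and with the unit on the laboratory report. Have the clinical lead confirm in writing the threshold that was intended. Then set the eligibility check in the database to the same number and unit.

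It would help to state in the same amendment whether exclusion criterion 6 covers categories A3 and B3 on the count alone or only clinical AIDS-defining conditions.

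The cost is a unit correction in two lines by amendment, one optional clarifying sentence, and one database check. Design, sample size and analysis are unchanged. This review takes no view on what the CD4 threshold should be.
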